#### **6.5 Replacement of individual subjects after withdrawal**

Withdrawn patients will be replaced by other patients matching the inclusion criteria.

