**SUMMARY**

**Rationale:** In earlier studies, we observed a positive correlation between vitamin D status and the regulation of the T cell compartment in MS patients.

**Objective:** The goal of this study is to assess whether supplementation of high doses vitamin D3 results in a promotion of T cell regulation. Meanwhile, the effectiveness in raising serum 25(OH)D levels, as well as the safety of this intervention with regard to calcium homeostasis will be monitored.

**Study design:** This is a cohort-study.

**Study population:** A total number of 15 participants will be included. These are interferon beta 1a or 1b-treated relapsing remitting MS patients older than 18 years, with a disease course shorter than 6 years. They have no disorders of the vitamin D hormonal system, or disorders which augment their susceptibility for hypercalcemia. Additionally, pregnant women will not take part in this study.

**Intervention (if applicable):** Patients will be supplemented with 500 µg vitamin D3/day in the form of Vigantol® (Merck™) solution for 12 weeks.

**Main study parameters/endpoints:** The effect of vitamin D supplementation on the T-cell compartment and in particular Treg function will be assessed. Secondly, serum 25(OH)D values, serum total calcium levels and kidney- and liver function will be monitored throughout the study.

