## 2. OBJECTIVES

Primary Objective:

- Does vitamin D3 supplementation with a dose of 500 µg/ day for 12 weeks result in an improved regulatory T cell function (i.e. reduction of ED50 in the *in vitro* assay) in relapsing remitting MS patients treated with interferon beta?

Secondary Objective(s):

- Does vitamin D3 supplementation with a dose of 500 µg/ day for 12 weeks result in a shift of the T cell compartment from a Th1 to a Th2 response in relapsing remitting MS patients treated with interferon beta?
- Is supplementation of vitamin D3 with a dose of 500 µg/ day for 12 weeks effective in raising 25(OH)D levels above 100 nmol/L in relapsing remitting MS patients treated with interferon beta?
- Is supplementation of vitamin D3 with a dose of 500 µg/ day for 12 weeks safe and tolerable in relapsing remitting MS patients treated with interferon beta?

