#### **6.4.1 Specific criteria for withdrawal (if applicable)**

Subjects will be withdrawn from the study if any of the following events occur:

- The reference values for serum total calcium are 2.10–2.55 mmol/L. If the serum total calcium level exceeds 2.55 mmol/L, the patient has to stop vitamin D supplementation until the measurement has been repeated. If the serum calcium level repetitively exceeds 2.55 mmol/L, the patient is withdrawn from the study. If not, the patient can continue the study.
- If liver- or kidney-function worsens clinically significant at week 6 when compared to baseline values, the patient will be withdrawn from the study and has to stop vitamin D supplementation immediately.

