#### **6.6 Follow-up of subjects withdrawn from treatment**

Subjects withdrawn from treatment, will have their safety measurements repeated at 2 weeks and 8 weeks after withdrawal from the study, to assess if their calcium levels normalise. The  $T^{1/2}$  of 25(OH)D is approximately 30 days.

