#### **6.7 Premature termination of the study**

The study will be terminated when more than 2 patients of the cohort experience a hypercalcaemia, or severe functioning of liver and/or kidney function as described in section 6.4.1.. All patients have to stop supplementation and will be followed as described in section 6.6.

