### **8.2 Univariate analysis**

The effect of the intervention on T cell characteristics (primary outcome measures) will be expressed as the difference between the respective continuous variables (ED50, T cell subsets or Th1/Th2 ratios) before and after treatment. The significance of this difference will be tested with a paired non-parametrical test (Wilcoxon ranking test). The same holds for the effect of the intervention on safety parameters and vitamin D metabolite values.

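### Patients withdrawn for calcium, liver or kidney findings are replaced, and the paired tests cannot use them; the protocol should keep them in the safety and 25(OH)D analyses

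*Protocol*

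**What the plan says.** The protocol's Summary sets the size: "A total number of 15 participants will be included". Section 6.5 adds that "Withdrawn patients will be replaced by other patients matching the inclusion criteria", whatever the reason for leaving.

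Section 6.4.1 lists the only mandatory reasons for withdrawal, and both are safety outcomes. For calcium: "If the serum calcium level repetitively exceeds 2.55 mmol/L, the patient is withdrawn from the study". For the organs: "If liver- or kidney-function worsens clinically significant at week 6 when compared to baseline values, the patient will be withdrawn from the study". Section 6.4 adds only the patient's own wish and the investigator's decision on urgent medical grounds.

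One secondary objective in section 2 asks whether the regimen is "safe and tolerable in relapsing remitting MS patients treated with interferon beta"; another asks whether it raises 25(OH)D above 100 nmol/L.

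Section 8.2 compares T cell outcomes before and after treatment with a paired Wilcoxon test and continues: "The same holds for the effect of the intervention on safety parameters and vitamin D metabolite values". Section 8.1 describes all data, presents biochemistry as continuous variables and rules out cut-offs.

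Two further provisions bear on the point. Withdrawn patients "will have their safety measurements repeated at 2 weeks and 8 weeks after withdrawal from the study" (6.6), and "The study will be terminated when more than 2 patients of the cohort experience a hypercalcaemia" (6.7, which also covers liver and kidney function).

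**The concern.** Having the safety outcome is itself what removes a patient and brings in a substitute. A patient withdrawn under 6.4.1 before the end of treatment has no end-of-treatment value, so the paired tests in 8.2 run on those who stayed. Because 8.1 bars cut-offs, the protocol also plans no count of calcium, liver or kidney events that would show the loss.

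The trial has one arm and a target of 15, so one or two patients visibly change the safety answer. If the report rests on the 15 who finished, a question about everyone given the regimen is answered only in those who tolerated 12 weeks of it. The primary ED50 comparison is selected in the same way, because its second sample is taken at week 12.

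**Working it through.** **What the rules imply together**

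1. Withdrawal under 6.4.1 depends on calcium, liver or kidney results, which section 6.1.2 names as the safety parameters.
2. Replacement under 6.5 is unconditional, so such a patient is followed by a new one.
3. For ED50, the pair is baseline and week 12 (6.3), so a patient withdrawn earlier cannot contribute.
4. For safety and 25(OH)D, 8.2 says only before and after. A withdrawn patient has control samples from weeks 2, 4 or 6 and safety measurements 2 and 8 weeks after withdrawal. The latter are taken off treatment to see whether calcium normalises (6.6). Used as the after value, they would measure recovery, not the effect under treatment.
5. With any replacement, more than 15 are dosed. Nothing says whether the replaced patients belong to the 15.

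**How many such replacements are possible**

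Section 6.7 stops the study at more than 2 patients, that is, at the third. If calcium, liver and kidney cases form one count, a completed study holds at most 2 replacements of this kind. If hypercalcaemia and liver/kidney cases are counted separately, which the wording also allows, the most is 2 + 2 = 4, or 4/19 = 21.1% of those dosed. Voluntary withdrawals are not capped.

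**What 1 or 2 replacements do to the figures**

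Exact (Clopper-Pearson) 95% limits for x of n: lower = Beta quantile 0.025 with parameters (x, n−x+1); upper = Beta quantile 0.975 with parameters (x+1, n−x). For 0/15 the upper limit is 1 − 0.025^(1/15) = 0.218.

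| Set | Events / patients | Rate | 95% CI |
|---|---|---|---|
| Completers only | 0/15 | 0% | 0 to 21.8% |
| All dosed, 1 replaced | 1/16 | 6.3% | 0.2 to 30.2% |
| All dosed, 2 replaced | 2/17 | 11.8% | 1.5 to 36.4% |

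For 25(OH)D above 100 nmol/L, suppose all completers succeed: 15/15 = 100% (78.2 to 100%). With two replaced patients added, the result is 15/17 = 88.2% (63.6 to 98.5%) if both fell short, or 17/17 if both exceeded 100. If the two withdrawn had the highest levels among 17, dropping them would lower the mean by about 0.2 SD (simulation, normal values assumed). The direction is therefore open.

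**How likely this is**

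The documents give no risk p of a 6.4.1 withdrawal, so p is assumed over a range. Patients are treated as independent and taken in order, with one combined count.

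- No such replacement: (1−p)^15.
- Stop before 15 complete: the third event comes before the 15th completer, so P(at least 3 events among 17).
- Complete after 1 or 2 replacements: the remainder.

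At p = 0.10:
- None: 0.9^15 = 0.206.
- Stop: 1 − (0.9^17 + 17 × 0.1 × 0.9^16 + 136 × 0.01 × 0.9^15) = 1 − (0.167 + 0.315 + 0.280) = 0.238.
- Complete after 1 or 2: 1 − 0.206 − 0.238 = 0.556.

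| Assumed p | None replaced | Complete after 1 or 2 | Stop first |
|---|---|---|---|
| 2% | 74% | 26% | 0.4% |
| 5% | 46% | 49% | 5% |
| 10% | 21% | 56% | 24% |
| 20% | 4% | 27% | 69% |

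**The case against.** The strongest reply is that no section excludes withdrawn patients from anything. Section 8.1 describes all data, 7.2 records all adverse events, 6.6 keeps measuring withdrawn patients, 6.7 counts hypercalcaemia in the cohort, and 7.2.2 requires a full safety analysis for the ethics committee. Replacement is a recruitment rule, and analysis sets may sit in an analysis plan that is not shown. This stands in part. A reader might infer that the safety tables must show 0% whatever the true rate; the documents do not support that, because nothing restricts the descriptive reporting to completers. What remains does not depend on an undefined set: unconditional replacement after outcome-driven withdrawal, combined with a paired test, is fixed in the protocol itself. Collecting data on withdrawn patients does not put them in a denominator.

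A reader might also infer that many events could be replaced unseen. At a 20% risk, 15/0.8 = 18.75 patients dosed would give 3.75 events. Section 6.7 would stop the study at the third on a combined count. Likewise, the 79% chance of at least one such withdrawal among the first 15 at 10% risk (1 − 0.9^15) includes studies that would be stopped. Section 5.3 regards the calcium risk as very low, and at 2% the chance of completing after a replacement is 26%.

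Finally, a reader might infer that 25(OH)D is flattered. If the highest responders are the ones withdrawn, the completers' mean falls, so the documents give no basis for a direction.

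**Conclusion.** The point holds as a conditional one. As written, sections 6.4.1, 6.5 and 8.2 together let patients with the safety outcome be replaced by patients without it in the paired comparisons, and 8.1 plans no event count to offset this. If completers are the analysed set, the safety objective is answered in a group selected for tolerance, and ED50 is selected in the same way. Actual bias in the descriptive safety report is not established.

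The size is modest in patients but material at n = 15: up to 0% against 11.8% in a completed study. This assumes one combined count in 6.7, and that hypercalcaemia there means the 2.55 mmol/L threshold of 6.4.1. Section 5.3 places pathological calcium above 2.60 mmol/L, so these passages need to be reconciled before the cap is certain. The probabilities of about 56% and 24% rest on an assumed 10% risk.

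Label: cheap improvement.

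**What to change.** Add to sections 6.5 and 8:

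- Replacement serves only to supply pairs for the ED50 analysis.
- Safety, tolerability and 25(OH)D are analysed in all patients who took at least one dose, using the last on-treatment 25(OH)D and the highest on-treatment calcium.
- Withdrawals under 6.4.1 are counted as events in that denominator, as a stated exception to the no-cut-off rule in 8.1.
- The ED50 result is reported with the number of withdrawals and their reasons.

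A sensitivity analysis that scores safety withdrawals as no improvement in ED50 is optional.

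The cost is wording and one extra analysis set. The data are already to be collected, since the Summary has 25(OH)D, calcium, kidney and liver function monitored throughout. Denominators rise slightly above 15 if anyone is replaced, and the safety figure may look slightly less favourable. Dosing, withdrawal and stopping rules are untouched.

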#### **6.6 Follow-up of subjects withdrawn from treatment**

Subjects withdrawn from treatment, will have their safety measurements repeated at 2 weeks and 8 weeks after withdrawal from the study, to assess if their calcium levels normalise. The  $T^{1/2}$  of 25(OH)D is approximately 30 days.

#### **6.7 Premature termination of the study**

The study will be terminated when more than 2 patients of the cohort experience a hypercalcaemia, or severe functioning of liver and/or kidney function as described in section 6.4.1.. All patients have to stop supplementation and will be followed as described in section 6.6.

## **7. SAFETY REPORTING**

### **7.1 Section 10 WMO event**

In accordance to section 10, subsection 1, of the WMO, the investigator will inform the subjects and the reviewing accredited METC if anything occurs, on the basis of which it appears that the disadvantages of participation may be significantly greater than was foreseen in the research proposal. The study will be suspended pending further review by the accredited METC, except insofar as suspension would jeopardise the subjects' health. The investigator will take care that all subjects are kept informed.

### **7.2 Adverse and serious adverse events**

Adverse events are defined as any undesirable experience occurring to a subject during a clinical trial, whether or not considered related to the supplementation of vitamin D3 by Vigantol® oil. All adverse events reported spontaneously by the subject or observed by the investigator or his staff will be recorded.

A serious adverse event is any untoward medical occurrence or effect that at any dose results in death;

- is life threatening (at the time of the event);
- requires hospitalisation or prolongation of existing inpatients' hospitalisation;
- results in persistent or significant disability or incapacity;
- is a congenital anomaly or birth defect;
- is a new event of the trial likely to affect the safety of the subjects, such as an unexpected outcome of an adverse reaction, lack of efficacy of an IMP used for the treatment of a life threatening disease, major safety finding from a newly completed animal study, etc.

All SAEs will be reported to the accredited METC that approved the protocol, according to the requirements of that METC.

#### **7.2.1 Suspected unexpected serious adverse reactions (SUSAR)**

Adverse reactions are all untoward and unintended responses to an investigational product related to any dose administered.

Unexpected adverse reactions are adverse reactions, of which the nature, or severity, is not consistent with the applicable product information in the Summary of Product Characteristics (SPC) of Vigantol® as provided by the manufacturer.

The sponsor will report expedited the following SUSARs to the METC:

- SUSARs that have arisen in the clinical trial that was assessed by the METC;
- SUSARs that have arisen in other clinical trial with Vigantol®, and that could have consequences for the safety of the subjects involved in the clinical trial that was assessed by the METC.

The remaining SUSARs are recorded in an overview list (line-listing) that will be submitted once every half year to the METC. This line-listing provides an overview of all SUSARs from the study medicine, accompanied by a brief report highlighting the main points of concern.

The expedited reporting will occur not later than 15 days after the sponsor has first knowledge of the adverse reactions. For fatal or life threatening cases the term will be maximal 7 days for a preliminary report with another 8 days for completion of the report.

### **7.2.2 Annual safety report**

In addition to the expedited reporting of SUSARs, the sponsor will submit, once a year throughout the clinical trial, a safety report to the accredited METC.

This safety report consists of:

- a list of all suspected (unexpected or expected) serious adverse reactions, along with an aggregated summary table of all reported serious adverse reactions, ordered by organ system, per study;
- a report concerning the safety of the subjects, consisting of a complete safety analysis and an evaluation of the balance between the efficacy and the harmfulness of the substance under investigation.

### **7.3 Follow-up of adverse events**

All adverse events will be followed until they have abated, or until a stable situation has been reached. Depending on the event, follow up may require additional tests or medical procedures as indicated, and/or referral to the general physician or a medical specialist.

## **8. STATISTICAL ANALYSIS**

### **8.1 Descriptive statistics**

All data will be analysed descriptively. The biochemical (vitamin D metabolite levels, calcium parameters, liver function tests, and kidney function tests) and immunological data (T cell subset percentages, percentage of Treg suppression) will be presented as continuous variables. No cut-off points will be used for any value. The demographical data will also be presented either as continuous or as categorical variables as appropriate. Of continuous data, medians and minimum-maximum ranges will be provided. Of categorical data, counts and corresponding percentages will be provided.

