25(OH)D in the serum reaches a plateau phase at 25(OH)D levels of 100 nmol/L (Hollis et al. 2007), indicating that the formation of 25(OH)D is sated at levels exceeding 100 nmol/L. Furthermore, adolescents with serum 25(OH)D levels >100 nmol/L were found to have a reduced risk for developing MS in later life, compared to adolescents with the lowest serum 25(OH)D values (Munger et al., 2006). With vitamin D therapy in this study, we aim for 25(OH)D levels exceeding these concentrations. In our recent study 'Vitamin D and the T cell compartment in multiple sclerosis' (NL 22666.096.07), 50% of RRMS patients with a short disease course had 25(OH)D levels <50 nmol/L, and only 3 patients exceeded the 100nmol/L. Interestingly, these three patients had all an optimal Treg function. These figures suggest that, when supplementing vitamin D in an attempt to modulate the immune response, vitamin D levels should exceed at least 100-150 nmol/L.

To determine the dose of vitamin D3 to reach these levels, one has to take safety into account. The only potential side effect of vitamin D supplementation, is decompensation of calcium metabolism and elevation of serum calcium values (hypercalcemia). Hypercalcemia has been rarely described in vitamin D3 supplemented subjects (Hathcock et al. 2007). The issue of safety will be specifically addressed in section 5.3. Two studies did assess the effect of vitamin D3 supplementation on 25(OH)D levels in MS patients. One study provided in weekly boluses the equivalent of 1000 µg/d, and reached a mean level of 325 nmol/L (min-max range 200-800 nmol/L) (Kimball et al. 2008). Another study supplemented patients with 250 µg/d for one year, reaching mean 25(OH)D levels of 413 nmol/L (min-max range 66 – 729) (Burton et al., 2008). Since we want to elevate 25(OH)D levels in all our patients at least above 100-150 nmol/L, we want to supplement our cohort with 500 µg/d. In several studies with vitamin D, it takes about 3 months for serum 25(OH)D levels to reach a new plateau phase. Therefore, subjects will receive 12 weeks supplementation.

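### Section 8.1 bars cut-offs for any value, although one secondary objective is attainment of 25(OH)D above 100 nmol/L and the protocol's own calcium limits are cut-offs

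*Protocol*

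**What the plan says.** **Objectives (Protocol, Section 2).** One secondary objective asks whether the dose is "effective in raising 25(OH)D levels above 100 nmol/L in relapsing remitting MS patients treated with interferon beta". Another asks whether it is "safe and tolerable in relapsing remitting MS patients treated with interferon beta", and gives no criterion.

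**Rationale (Section 1).** The dose is justified by an aim for every patient: "Since we want to elevate 25(OH)D levels in all our patients at least above 100-150 nmol/L".

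**Descriptive analysis (Section 8.1).** Vitamin D metabolites and calcium, liver and kidney values are presented as continuous variables. Then: "No cut-off points will be used for any value". The summary is fixed as well: "Of continuous data, medians and minimum-maximum ranges will be provided".

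**Testing (Section 8.2).** The primary outcome is tested as a before-after difference with a paired Wilcoxon test. The section then adds: "The same holds for the effect of the intervention on safety parameters and vitamin D metabolite values".

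**Calcium limits used in conduct.**
- Section 5.3 calls total calcium above 2.60 mmol/L pathological.
- Section 6.4.1 interrupts supplementation above 2.55 mmol/L and withdraws the patient if the excess is repeated.
- Section 6.5 replaces withdrawn patients.
- Section 6.7 ends the study when more than 2 patients have hypercalcaemia.

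**The concern.** An objective worded as passing 100 nmol/L calls for the number of patients who pass it. Section 8.1 does not merely leave that count to a later document. It rules the count out, so a statistical analysis plan that included it would depart from the protocol. The Wilcoxon test in Section 8.2 asks whether values moved from baseline, which is a different question.

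Safety has a similar mismatch. Sections 5.3, 6.4.1 and 6.7 treat harm as individual patients crossing a calcium limit, whereas the planned test looks at the typical change. At stake is what the report can say: a significant rise in 25(OH)D without the number who reached the target, and a calcium p-value that says little about hypercalcaemia in either direction.

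**Working it through.** **Inputs.** From the protocol: 15 patients in a single arm, the 100 nmol/L target, calcium limits of 2.55 and 2.60 mmol/L, and termination at more than 2 hypercalcaemic patients. The protocol gives no figure of its own for the 25(OH)D or safety objectives (Section 4.4 sizes the study on ED50), so there is nothing to reproduce. All patient values below are constructed, and the SD of calcium change is an assumption.

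**1. The test does not see 100 nmol/L.** If all 15 differences are positive, the exact two-sided Wilcoxon p is 2/2^15 = 0.00006, whatever levels are reached. Example: baseline values from 25 to 60, rises of 10 to 35, week-12 median 65 and maximum 95 nmol/L. Then p = 0.00006 and 0/15 are above 100.

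**2. Median and range do not give the count.** Two sets of 15 week-12 values:
- Set A: 60, 70, 80, 85, 90, 95, 98, 105, 106, 107, 108, 109, 110, 111, 400.
- Set B: 60, 101, 101.5, 102, 102.5, 103, 104, 105, 106, 107, 108, 109, 110, 111, 400.

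Both have median 105, minimum 60 and maximum 400. With baselines evenly spaced from 25 to 55, every patient rises in both sets, so both give the same exact p of 0.00006. Set A has 8/15 above 100 (exact 95% CI 26.6 to 78.7%) and set B has 14/15 (68.1 to 99.8%). The planned output cannot tell them apart.

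This in-between case is not far-fetched. Section 1 cites an MS study at 250 µg/day with a mean of 413 nmol/L and a range starting at 66. Such a summary shows that not every value passed 100, but not how many failed to.

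**3. The test on calcium can mislead both ways.**
- *Significant without hypercalcaemia.* Baselines from 2.22 to 2.40 mmol/L and rises of 0.01 to 0.05 in all 15 give a maximum of 2.45, nobody above 2.55, and p = 0.00006.
- *Not significant with three large rises.* Three patients rise by 0.35, 0.40 and 0.45 mmol/L. Twelve have changes of alternating sign, from 0.010 to 0.032 in size. The positive ranks sum to (13 + 14 + 15) + (1 + 3 + 5 + 7 + 9 + 11) = 78 and the negative ranks to 2 + 4 + 6 + 8 + 10 + 12 = 42, so p = 0.33. Three is the count at which Section 6.7 ends the study, if these patients are hypercalcaemic.

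**4. Sensitivity by simulation.** n = 15, 4,000 runs, k patients shifted by +0.30 mmol/L and the rest centred on zero. For an SD of change from 0.05 to 0.10 mmol/L, the test is significant in about 8 to 9% of runs for k = 2 and about 15 to 16% for k = 3, against a nominal 5% with no effect. The choice of SD matters little in this range. A rise of 0.30 passes 2.55 only from a baseline above 2.55 − 0.30 = 2.25, and passes 2.60 only from above 2.30.

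**5. What counts would show at n = 15 (exact 95% CI).**

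| Result | Percentage | 95% CI |
|---|---|---|
| 15/15 above 100 nmol/L | 100% | 78.2 to 100% |
| 13/15 above 100 nmol/L | 86.7% | 59.5 to 98.3% |
| 0/15 above calcium limit | 0% | 0 to 21.8% |
| 2/15 above calcium limit | 13.3% | 1.7 to 40.5% |

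The limit for 0/15 is 1 − 0.025^(1/15) = 21.8%.

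**The case against.** A reader might infer that the plan cannot answer either objective at all. The documents do not support that. The Wilcoxon test is added to the descriptive summaries and does not replace them. The minimum and maximum do part of the work: a week-12 minimum above 100 nmol/L would confirm the all-patients aim of Section 1, a maximum below 100 would show that nobody reached it, and a calcium maximum at or below the limit would show no reported excess. What is lost is the number of patients in between.

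A reader might also infer that hypercalcaemia could pass unnoticed. It could not. Section 6.4.1 acts on each raised value, Section 6.7 ends the study on a count, Section 7.2 records all adverse events, and Section 7.2.2 requires a complete safety analysis in the yearly report. Read in place, the sentence in 8.1 governs how values are presented and does not switch off these rules.

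Three further limits are fair. The safety objective itself names no threshold. The protocol does not say that a non-significant Wilcoxon result will be taken as proof of safety. And Section 8.2 names no visit, while the descriptive plan is not confined to week 12, so the calcium values at weeks 2, 4 and 6 cannot be called excluded from the report.

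The simulation also keeps the affected patients among the 15 pairs, whereas Sections 6.4.1 and 6.5 would withdraw and replace those with a repeated excess. That weakens the simulation as a model of this trial, but it does not rescue the test. The protocol does not say whether withdrawn patients stay in the analysis, and if they do not, a before-after comparison would miss them altogether.

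What remains is a contradiction in the text on 25(OH)D and a poorly suited test for safety.

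**Conclusion.** The point holds in a limited form. The no-cut-off sentence contradicts the 100 nmol/L objective outright and sits badly with the calcium limits that the protocol uses elsewhere. The Wilcoxon test does not directly answer the 25(OH)D question, and it is a poor measure of hypercalcaemia in individuals: under the assumed SD of 0.05 to 0.10 mmol/L it would flag 2 or 3 affected patients in roughly 8 to 16% of trials. The argument that the test and the range do not yield a count needs no assumption about variability; only the detection rates do.

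This should be fixed but does not threaten the trial. The primary endpoint, the sample size and the safety conduct are unaffected, and no new data are needed.

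**What to change.** 1. Delete the no-cut-off sentence in Section 8.1, or restrict it to the immunological data.
2. Report the number and percentage with 25(OH)D above 100 nmol/L at week 12, with an exact 95% CI and a stated denominator.
3. Report the number and percentage of all treated patients, including those withdrawn and replaced, with any post-baseline total calcium above the protocol limit, with an exact 95% CI. Add each patient's highest value. With replacements the denominator may exceed 15.
4. State that no safety conclusion rests on the Wilcoxon p-value.
5. The sponsor must reconcile the 2.55 mmol/L of Section 6.4.1 with the 2.60 mmol/L of Section 5.3, so that item 3 has one definition.

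The cost is some wording and one extra table. The safety statement will look less favourable because its imprecision becomes visible: even 0/15 leaves an upper limit of 21.8%.
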